### Safety and AE Monitoring

In this trial, safety will be monitored, including AEs, serious AEs, and withdrawals due to AEs. The safety indexes are mainly composed of the routine blood, liver function, kidney function, coagulation function and vital signs. AEs of latamoxef mainly include anaphylaxis (such as rashes, urticaria, and itching), gastrointestinal reactions (such as vomiting, diarrhea and abdominal pain), and other latamoxef associated AE (such as anaphylactic shock, elevated levels of aminotransferases and serious bleeding).

### Sample Size Estimates

According to our preliminary PPK study and dose simulation for latamoxef in neonates (Qi et al., 2019), 60.2% of neonates using conventional treatment regimen (30 mg/kg q12 h) reached 70% fT > MIC and 80.1% of neonates using model treatment regimen (20 mg/kg q8h) reached 70% fT > MIC with MIC of 2 mg/L, respectively. We conducted sample size estimation for superiority design by using PASS 15.0 (NCSS, Kaysville, Utah, United States). To achieve a statistical power of 80% (one-sided type 1 error of 5%), the calculated sample size of each treatment group was 57 patients per treatment group (114 in total) with the ratio of 1:1. Taking into account a 10% dropout rate, 64 patients per treatment group (128 in total) will be required.

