### Study Data and Statistical Analysis Plan

The procedures and contents of data collection for this trial are detailed in Table 2. Demographic information, diagnosis, clinical data and laboratory data at baseline will be recorded on electronic case report form (eCRF) platform provided by Six Yuan (Table 2). In addition, clinical data, laboratory data and AEs at every planed time point after initiation of treatment will also be recorded in this eCRF platform (Table 2). According to the data collection methods and standards formulated by project director and researchers, all data of eCRF platform will be recorded in a true, detailed and careful manner to ensure the authenticity of the data.

Statisticians, independent of all the other processes, will conduct the statistical analyses by using SPSS version 15.0 for Windows (Chicago, IL, United States). The statisticians will calculate the mean, standard deviation, median, minimum, maximum, lower quartile (Q1), upper quartile (Q3) for quantitative data and describe numbers and percentages for qualitative data (Wang et al., 2020). Comparisons between two groups will be conducted as following: t-tests or Wilcoxon rank-sum for normal or nonnormal ability distributions for quantitative data; chi-square test or Fisher’s exact test for qualitative data (Wang et al., 2020). Analysis for missing data performed on the intention-to-treat principle. For all analysis, *p* value < 0.05 will be considered statistically significant.

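### The stated 57 infants per group does not give 80% power: the protocol's own inputs need 63 to 65, and 57 gives about 76%

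*Protocol article*

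**What the plan says.** All the planning inputs are in the Sample Size Estimates section of the protocol article. The two rates come from the group's earlier pharmacokinetic model and dose simulation: "60.2% of neonates using conventional treatment regimen (30 mg/kg q12 h) reached 70% fT > MIC". The corresponding figure for the model regimen is 80.1%, and both are taken at an MIC of 2 mg/L. The software and type of comparison are given as "We conducted sample size estimation for superiority design by using PASS 15.0", and no margin is mentioned. Power is 80% and the type 1 error is 5%, one-sided. The result is that "the calculated sample size of each treatment group was 57 patients per treatment group (114 in total) with the ratio of 1:1". The dropout step follows: "Taking into account a 10% dropout rate, 64 patients per treatment group (128 in total) will be required".

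The Study Data and Statistical Analysis Plan section names the analysis for binary outcomes as "chi-square test or Fisher’s exact test for qualitative data". It sets the threshold as a p "value < 0.05 will be considered statistically significant", without saying whether the test is one- or two-sided.

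**The concern.** Two rates, a one-sided error rate, a power and a 1:1 allocation are enough to fix a two-proportion sample size to within a few patients, whichever standard formula is used. All of these are printed, so the figure can be checked without the full protocol or the analysis plan. A first calculation gives a number in the low to middle sixties, not 57.

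At stake is the stated power of the primary comparison. Readers and ethics reviewers take from this section that a true difference of the planned size would be missed one time in five. If 57 is too few, the risk is higher than stated, and the dropout-adjusted enrolment figure built on 57 inherits the error.

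**Working it through.** **Inputs** (all from Sample Size Estimates)

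- p1 = 0.602 (conventional), p2 = 0.801 (model), so d = 0.199.
- Mean rate p̄ = (0.602 + 0.801)/2 = 0.7015.
- One-sided alpha 0.05: z = 1.6449. Power 0.80: z = 0.8416. Squared sum: (1.6449 + 0.8416)² = 6.1826.
- d² = 0.039601.
- V1 = p1(1 − p1) + p2(1 − p2) = 0.239596 + 0.159399 = 0.398995 (square root 0.63166).
- V0 = 2p̄(1 − p̄) = 0.418796 (square root 0.64714).

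**Sample size per group for 80% power**

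- Unpooled z-test: n = 6.1826 × V1/d² = 6.1826 × 0.398995/0.039601 = 62.29, so **63**.
- Arcsine: h = 2·asin√0.801 − 2·asin√0.602 = 0.44056; n = 2 × 6.1826/h² = 63.71, so **64**.
- Pooled z-test (matches the uncorrected chi-square): n = (1.6449 × 0.64714 + 0.8416 × 0.63166)²/d² = 64.33, so **65**.
- Continuity-corrected: n = (64.33/4) × [1 + √(1 + 4/(64.33 × 0.199))]² = 74.04, so **75**.

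Other variants are further from 57: pooled variance under both hypotheses 65.4 (66), log odds ratio 67.4 (68), log risk ratio 68.9 (69). A two-sided 5% test needs 80 (unpooled) or 82 (pooled). None of the methods tried returns 57; the nearest is 63.

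**Power at 57 per group, one-sided 5%**

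- Unpooled: d√57/√V1 − 1.6449 = 0.199 × 7.5498/0.63166 − 1.6449 = 0.734, so power is **76.8%**.
- Pooled: (0.199 × 7.5498 − 1.6449 × 0.64714)/0.63166 = 0.693, so power is **75.6%**.
- Exact binomial enumeration: 75.7% for the pooled z-test, 76.9% for the unpooled z-test, 69.4% for Fisher's exact test.

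**Dropout step**

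- The step itself is right: 57/0.9 = 63.3, rounded up to 64.
- With 64 enrolled and 10% lost, 64 × 0.9 = 57.6 per group remain, and power is 76.0% (pooled) to 77.2% (unpooled).
- From the correct base: 63/0.9 = 70, 64/0.9 = 71.1 (72), 65/0.9 = 72.2 (73) enrolled per group.

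**Where 57 might come from**

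- Entering 81.0% instead of 80.1% gives 56.23 with the unpooled formula, so 57. The arcsine and pooled formulas then give 57.61 (58) and 58.27 (59).
- The pooled formula with the printed rates returns 57 at 75% power.
- Either slip is possible. The document does not show which, if either, occurred.

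**The case against.** **An unprinted option in the software could explain 57.** The article names PASS 15.0 but not the procedure. The plausible alternatives, however, all push the number up: a two-sided test, Fisher's exact test, a continuity correction, or a superiority margin above zero. For 57 to give 80% power, the one-sided alpha would have to be about 0.06 to 0.07, which contradicts the stated 5%. This objection fails.

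**The dropout allowance covers the shortfall.** With 64 per group and no losses, power would be 79.8% (pooled) to 80.9% (unpooled). But the allowance is there to be used up by the 10% loss that the protocol itself expects. This fails too.

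**The shortfall is small and the inputs are soft.** This has some force. The gap is 3 to 4 points of power, and it touches neither the type 1 error nor the validity of the comparison. The rates are simulation outputs, and a change of 0.9 points in one of them moves the unpooled requirement from 63 to 57. That limits how much weight any exact figure can bear. It does not make the printed power correct for the printed rates.

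**The 81.0% explanation is a guess.** That is right. It works only with the unpooled formula, and other slips fit as well. It is a reason to check the software entries, and the finding does not depend on it.

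**Conclusion.** The stated sample size is wrong for the stated inputs. The requirement is 63 to 65 evaluable infants per group (126 to 130 in total), so 57 is 6 to 8 per group short. At 57 the one-sided power is about 76% (75.6% to 76.8%), and the chance of missing the planned difference is about 24% instead of 20%.

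This rests on the printed rates, a one-sided 5% test, zero margin, equal allocation and an uncorrected two-proportion test, which is the reading kindest to the plan. If Fisher's test is used, one-sided power at 57 is 69.4%. If the p-value threshold is meant as two-sided, pooled power at 57 is 64.4%.

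The size also assumes that 64 per group are enrolled. The Abstract and the Trial Design section give 114 as the number expected or to be enrolled. If 114 were the enrolment total and 10% were lost, 51.3 per group would remain and power would be about 72% (pooled) to 73% (unpooled).

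**What to change.** Change the Sample Size Estimates section in one of two ways.

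1. Keep the numbers and restate the power: 57 evaluable infants per group give about 76% power, at a one-sided 5% level, for 60.2% versus 80.1%. This costs one sentence and a slightly less favourable figure, with no extra patients.
2. Keep the 80% claim and restate the requirement: 63 to 65 evaluable per group according to the test chosen, hence 70 to 73 enrolled per group with 10% dropout (140 to 146 in total, against 128 now).

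In both cases name the test behind the calculation, since the answer depends on it, and check the PASS inputs and procedure, in particular the second proportion.

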### Study Data and Statistical Analysis Plan

The procedures and contents of data collection for this trial are detailed in Table 2. Demographic information, diagnosis, clinical data and laboratory data at baseline will be recorded on electronic case report form (eCRF) platform provided by Six Yuan (Table 2). In addition, clinical data, laboratory data and AEs at every planed time point after initiation of treatment will also be recorded in this eCRF platform (Table 2). According to the data collection methods and standards formulated by project director and researchers, all data of eCRF platform will be recorded in a true, detailed and careful manner to ensure the authenticity of the data.

Statisticians, independent of all the other processes, will conduct the statistical analyses by using SPSS version 15.0 for Windows (Chicago, IL, United States). The statisticians will calculate the mean, standard deviation, median, minimum, maximum, lower quartile (Q1), upper quartile (Q3) for quantitative data and describe numbers and percentages for qualitative data (Wang et al., 2020). Comparisons between two groups will be conducted as following: t-tests or Wilcoxon rank-sum for normal or nonnormal ability distributions for quantitative data; chi-square test or Fisher’s exact test for qualitative data (Wang et al., 2020). Analysis for missing data performed on the intention-to-treat principle. For all analysis, *p* value < 0.05 will be considered statistically significant.

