### Randomization and Blinding

To minimize selective bias, Beijing Six Yuan Space Information Technology Co., Ltd (Six Yuan) has been entrusted to conduct a stratified blocked randomization by using a computer random number generator in the system of Six Yuan. Participants will be randomly divided into the conventional treatment group and the model treatment group with a ratio of 1:1. The randomized code of the trial, derived from the random system of Six Yuan, will be the unique identification code of participants. After assignment of the randomization code, researchers are un-blinded to the treatment regimen of latamoxef. Considering that the drug concentration detection and data analysis will significantly affect the conclusion of this trial, all the research assistants in charge of drug concentration detection and statisticians will be blinded to treatment assignment until the trial is completed.

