#### Secondary Outcomes

This trial has five secondary outcomes:1) Rate of latamoxef treatment failure: the symptoms and laboratory indicators of infection persist or worsen after latamoxef treatment. Neonatologists have to increase of the dose of latamoxef, or add other antibiotics to the treatment with latamoxef, or stop latamoxef treatment and switch to other antibiotics.2) Duration of antibiotic therapy: the length of antibiotic therapy for EONS;3) Changes of white blood cell count (WBC), CRP and PCT: comparison of the changes of WBC, CRP and PCT at baseline, initial stage of treatment (18–72 h) and before the end of treatment (Table 3);4) Blood culture results during administration: comparison of blood culture results at baseline, initial stage of treatment (18–72 h) and before the end of treatment (Table 3);5) Incidence of adverse events (AE)s: monitoring and recording AEs during latamoxef therapy (Table 3).

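### Randomisation is stratified but the planned tests are not, and WBC, CRP and PCT changes are compared without baseline adjustment: precision is lost if strata or baseline values are prognostic

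*Protocol article*

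**What the plan says.** Under Randomization and Blinding, the protocol article says an outside company will "conduct a stratified blocked randomization by using a computer random number generator". It does not name the stratification factors.

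Under Study Data and Statistical Analysis Plan, every two-group comparison is one of two kinds: a t-test or Wilcoxon rank-sum test for quantitative outcomes, and "chi-square test or Fisher’s exact test for qualitative data". No stratified or covariate-adjusted analysis appears. The section refers to p values below 0.05 and mentions no confidence interval.

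The primary outcome falls under the second kind, because Sample Size Estimates treats it as a proportion attaining the target in each arm: "60.2% of neonates using conventional treatment regimen (30 mg/kg q12 h) reached 70% fT > MIC" against "80.1% of neonates using model treatment regimen (20 mg/kg q8h) reached 70% fT > MIC with MIC of 2 mg/L".

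Under Secondary Outcomes, the inflammatory markers are assessed by "comparison of the changes of WBC, CRP and PCT at baseline, initial stage of treatment (18–72 h) and before the end of treatment". Table 3 schedules blood routine (which includes white cells), CRP and PCT at baseline and at both later stages.

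**The concern.** Stratified randomisation balances the arms within strata and so removes between-stratum variation from the arm difference. An unstratified chi-square or Fisher test still counts that variation in its standard error. If the strata predict the outcome, the standard error is too large, the true type I error falls below nominal and power is lost.

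For WBC, CRP and PCT, a change score subtracts the whole baseline value whatever its correlation with follow-up. When that correlation is moderate, the subtraction adds noise that regression on baseline would avoid.

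At stake is precision: some power for the primary comparison, and wider uncertainty than necessary for one of the five secondary outcomes.

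**Working it through.** **The plan's own figure.** Inputs from Sample Size Estimates: 60.2% and 80.1%, one-sided 5%, 80% power, "57 patients per treatment group (114 in total) with the ratio of 1:1". The unpooled formula gives (1.645 + 0.842)² × (0.602×0.398 + 0.801×0.199) / 0.199² = 62.3, so 63 per arm; the pooled formula gives 65. The stated 57 is not reproduced. Exact enumeration at 57 per arm gives 75.7% power with the unstratified pooled test. That discrepancy is a separate matter; here 57 per arm and about 76% serve only as the starting point.

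**Why the unstratified test is conservative: a two-stratum illustration.** Assume two equal strata averaging 55% and 85% attainment (assumed; the overall mean of 70% matches the planned average).
- Within-stratum variance: (0.55×0.45 + 0.85×0.15)/2 = 0.1875.
- Variance used by the unstratified test: 0.70×0.30 = 0.21.
- Ratio 0.1875/0.21 = 0.893; SE ratio √0.893 = 0.945.
- True size at nominal one-sided 5%: 1 − Φ(1.645/0.945) = about 4.1%. At nominal two-sided 5%: 2[1 − Φ(1.96/0.945)] = about 3.8%.

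**Power over a range of stratum effects.** Simulation of 200,000 trials, 57 per arm, three equal strata, overall rates near 60% and 80%, one-sided 5%. All spreads are assumed.

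| Control-arm rates by stratum | Chi-square power | CMH power | Gain (points) | Chi-square type I error | Unadjusted SE vs stratified SE |
|---|---|---|---|---|---|
| 60/60/60% | 75.7% | 75.9% | 0.2 | 5.2% | about equal |
| 48/61/72% | 76.0% | 77.1% | 1.1 | 4.8% | +1% |
| 37/62/81% | 77.2% | 80.6% | 3.4 | 3.9% | +6% |
| 28/64/89% | 78.3% | 84.3% | 6.0 | 2.9% | +13% |

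The Cochran-Mantel-Haenszel (CMH) type I error stays between 4.9% and 5.2% throughout. A still more extreme spread (21/66/94%) gives 79.7% against 88.6%, but nothing in the article suggests strata that far apart.

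The analysis section does not state sidedness. With a critical value of 1.96, the four rows become 65.6 vs 65.2%, 65.8 vs 66.3%, 66.8 vs 70.3% and 67.4 vs 75.4%. The pattern is the same: essentially nothing for absent or weak strata, and several points for strong ones.

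**Biomarkers.** Let σ² be the common variance at baseline and follow-up and r their correlation. The article gives neither.
- Change-score variance: 2σ²(1 − r).
- ANCOVA residual variance: σ²(1 − r²).
- Ratio: (1 + r)/2.

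| Assumed r | Variance ratio | Reduction | SE ratio | 80% two-sided power becomes |
|---|---|---|---|---|
| 0.3 | 0.65 | 35% | 0.81 | about 94% |
| 0.5 | 0.75 | 25% | 0.87 | about 90% |
| 0.7 | 0.85 | 15% | 0.92 | about 86% |

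With unequal standard deviations σ₀ and σ₁, the change-score variance exceeds the ANCOVA variance by (σ₀ − rσ₁)², which is never negative. Apart from the small cost of estimating the slope, ANCOVA does not lose.

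**The case against.** The strongest reply is that this is an efficiency preference and not an error. The unadjusted test does not inflate type I error or bias the estimate, and under randomisation any baseline imbalance is chance. That stands.

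The second reply is that the loss is hypothetical. The strata are unnamed. If the stratum is hospital, the article does not link hospital to attainment; the clearance covariates in the Introduction are current weight, birth weight and postnatal age, dosing is per kilogram, and eligibility already limits age to 3 days and gestation to at least 32 weeks. This also stands, which is why the gain is given as a range starting near zero. The other side of the argument is that weight and maturity still vary from 32 weeks to term and could differ between strata, and that stratifying costs almost nothing when they do not matter.

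The third reply is that such detail belongs in an analysis plan that is not shown. That carries less weight: the article itself names the between-group tests, so this is a stated choice and not a gap.

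A reader might infer more than the text supports:
- That the baseline WBC, CRP and PCT values are ignored. They are not; Secondary Outcomes compares changes, which use the baseline, though inefficiently.
- That reported intervals will be too wide in all cases. No confidence intervals are mentioned, and the standard error is inflated only if the strata are prognostic.
- That the arms converge by design at the last measurement because these markers decide when treatment stops. The article gives no such stopping rule; laboratory indicators appear only in the definition of treatment failure.

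**Conclusion.** The point holds as an avoidable loss of precision and not as a threat to validity. The stated analysis does not follow the stratified design. For the primary outcome at 57 per arm and one-sided 5%, the cost is about 0 to 1 point of power if the strata are not or only weakly prognostic, and 3 to 6 points if strongly prognostic. This rests on assumed stratum spreads and three equal strata. For WBC, CRP and PCT, change scores have more variance than ANCOVA for any r below 1 when variances are equal; the ANCOVA reduction is 15% to 35% for assumed r from 0.7 down to 0.3. The biomarker figures describe mean comparisons on a suitable scale; they do not carry over directly to a Wilcoxon test. The change should be made because it is free, not because the planned tests would mislead.

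**What to change.** - Name the randomisation strata and use those same strata in the analysis.
- Primary outcome: Cochran-Mantel-Haenszel test, with a stratified risk difference and its confidence interval.
- Treatment failure and adverse events: the same approach where counts allow; otherwise keep Fisher's exact test and say so in advance.
- WBC, CRP and PCT: ANCOVA of the follow-up value on baseline, treatment and strata, on the log scale where the distribution is skewed, in place of t-tests or Wilcoxon tests on changes.

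The cost is a few lines of analysis-plan wording, fixed before unblinding, and routine programming. The baseline measurements are already scheduled in Table 3 and the strata must exist in the randomisation system, so no new data are needed.

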### Quality Control

In order to ensure the quality of the trial, project director and researchers from each hospital have formulated detailed project implementation protocol and emergency plan at the beginning of this trial. During the clinical trial, researchers participating in this experiment shall undergo unified training to clarify and unify the recording methods and standards for data collection on the eCRF platform. Moreover, the clinical inspector, designated by the director, will make an inspection tour to each hospital periodically to ensure that the researchers strictly adhere to the clinical trial protocol and fill in the information correctly.

## Discussion

In our proposed study, based on our preliminary PPK-PD analysis of latamoxef in neonates, we are aimed to conduct a single-blind, multicenter RCT and compare the 70%fT > MIC, efficacy and safety between conventional regimen and PPK model regimen for latamoxef in EONS treatment for the first time. Our study will provide PD data for optimizing latamoxef usage in EONS treatment.

EONS, a serious threat for health of neonates, is mainly caused by bacterial pathogens transmitted vertically from mother to infant before or during delivery (Hornik et al., 2012). The organisms involved in EONS are not identical in different countries and regions. In the developed countries, *Group B Streptococcus* (*GBS*) and *Escherichia coli* (*E. coli*) are most frequently bacteria; in China, *E. coli* and *Coagulase-negative staphylococcus* (*CONS*) were the leading pathogenic bacteria (Jiang et al., 2019), followed by *Achromobacter xylosoxidans* (*A. xylosoxidans*) and *Klebsiella pneumoniae* (*K. pneumoniae*). Therefore, broad-spectrum cephalosporins are often used as an important anti-infective drug in the Chinese EONS treatment, such as latamoxef. However, due to the limited PK and PD neonatal data, the dosing guidelines and optimal treatment regimen of latamoxef cannot be applied in EONS treatment.

To ensure that the finding of this trial can comprehensively reflect PD characteristics of latamoxef in EONS treatment, 70% fT > MIC will be used as the primary outcome indicator, and efficacy and safety indexes will be employed as the secondary outcome indicators. Because there’s no clinical evaluation of latamoxef in EONS treatment, the trial design is derived from other clinical trials about cephalosporin treatment or therapeutic decision conducted in children or neonates (Stocker et al., 2017; Wu et al., 2020). Rate of treatment failure, duration of antibiotic therapy, changes of inflammatory indicators, results of blood culture and incidence of AEs are commonly used indicators in efficacy and safety evaluation for anti-infective agents (Molyneux et al., 2011; Stocker et al., 2017). Since latamoxef is an oxacephem antibiotic that imparts time-dependent bactericidal effects, fT > MIC as a PD parameter is essential for efficacy evaluation of latamoxef. Although 40–50% fT > MIC is usually used in adult antimicrobial treatment, a goal of 70% fT > MIC is considered as a more conservative endpoint for avoiding treatment failure in immunologically immature neonates (Craig, 1995; Craig, 2001).

According to the bacterial susceptibility data of latamoxef in relation to the bacteria commonly observed in Chinese EONS patients, the MIC90 values of *E. coli* and *K. pneumoniae* were 1 mg/L and 2 mg/L (Cui Lan-Qing, 2016). Thus, 70% fT > MIC targets in two treatment regimens with MIC of 2 mg/L were applied as parameters in sample size calculation.

Our study had some limitations. First, since EONS patients often improve or recover at hospital discharge, follow-up is not designed in this trial. Hence our efficacy evaluation may miss some relapse situation after hospital discharge. Second, due to the few positive culture results and antimicrobial susceptibility results of bacteria in neonatal clinical practice, we chose 70% fT > MIC target with MIC of 2 mg/L in sample size calculation based on epidemiological microbiology data instead of individual microbiology. Finally, our study data are only from Chinese EONS patients in Beijing, limiting the generalizability to other populations and areas with different epidemiological microbiology data.

We hoped that our study can provide reliable data to support rational use of latamoxef in EONS treatment.
